### Data analysis

We will present the numbers of the recruitment and measurement procedure in the CONSORT extension to randomised pilot and feasibility trials flow diagram (Fig. 6). We will report the participant characteristics and the baseline descriptives for each participant.

**Fig. 6 Fig6:**
[figure not shown]
The Consolidated Standards of Reporting Trials (CONSORT) extension to randomised pilot and feasibility trials flow diagram [27]

ChARMin data will be processed by a custom-made Matlab algorithm (The MathWorks Inc.). Statistical analysis will be performed with IBM SPSS Statistics 24.

In case of incomplete datasets, loss to follow-up or if a participant would be treated in the other treatment group than the one he or she was allocated to, we plan an intention-to-treat analysis. In case of missing data (e.g. a participant is not able to attend a session), we plan to perform a multiple imputation by chained equation.

#### Analysis of feasibility

The ten areas (see outcome measures section) will be evaluated with the information obtained during the study. Only questions 8, 9 and 10 will require statistical analyses to be answered:
8)Responsiveness analysis of the outcome measures for this specific intervention: the data (MA2_fluency_ and exergame test data) of the measurement time point immediately before the first and right after the last practice session will be compared. For internal responsiveness, the standardised response mean will be calculated. For the external responsiveness, a Pearson correlation coefficient will be calculated between the change-scores (i.e. between the two measurement time points) of the MA2_fluency_ and the ChARMin parameter nP_norm_.9)Effect due to the parallel therapies within the rehabilitation setting: We will include data of all participants to test for a significant change in exergame and MA2fluency scores between day 1 and day 3 in week 1 (i.e. without specific intervention, see Fig. 4) using a paired *T* test or Wilcoxon signed-rank test if a non-parametric analysis will be required. Assuming that the participants will have similar therapy schedules during week 1 and 2, and no change is measured during week 1, a change during week 2 could be attributed to the robotic training. However, if outcomes will improve significantly in week 1, changes observed during week 2 will need to be interpreted with caution, as they cannot be attributed to the study’s intervention alone.10)The sample size estimation for the main trial will be calculated according to the formula

$$ n=\frac{{\left({Z}_{\alpha }+{Z}_{\beta}\right)}^2\times 2{\sigma}^2}{{\left({\mu}_1-{\mu}_2\right)}^2}\kern0.75em $$[46].

Where *n*= sample size, *Z*_*α*_= standard normal *z* value for a significance level *α* = 0.05, which is 1.96, *Z*_*β*_ = standard normal *z* value for the power of 80%, which is 0.84. The pooled standard deviation of the pre-and post-intervention differences (both groups) is indicated by *σ*, *μ*_1_ is the mean pre-post-intervention difference of the intervention group 1, *μ*_2_ is the mean pre-post-intervention difference of the intervention group 2.

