**Methods:**

Children with affected upper limb function due to congenital or acquired brain lesions undergoing neurorehabilitation will be recruited for a randomised controlled pilot study with a 3-week procedure. In the control week (1), two assessment blocks (robot-assisted reaching tasks, Melbourne assessment 2, subscale fluency), 2 days apart, take place. In the practice week (2), participants are randomly allocated to blocked practice or random practice and perform 480 reaching and backward movements in the horizontal and vertical plane using exergaming with an exoskeleton robot per day during three consecutive days. Assessments are performed before, directly after and 1 day after the practice sessions. In the follow-up week (3), participants perform the assessments 1 week after the final practice session. The primary outcome is the immediate transfer of the Melbourne Assessment 2, subscale fluency. Secondary outcomes are the immediate retention, 1-day and 1-week delayed transfer and retention and acquisition during the practice sessions. We will evaluate the feasibility of the inclusion criteria, the recruitment rate, the scheduling procedure, the randomisation procedure, the procedure for the participants, the handling of the robot, the handling of the amount of data, the choice of the outcome measures and the influence of other therapies. Furthermore, we will perform a power calculation using the data to estimate the sample size for the main trial.

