### Setting

The study will take place at the Swiss Children’s Rehab of the University Children’s Hospital Zurich in Affoltern am Albis, Switzerland. All measurements and practice sessions will be performed during a multidisciplinary in-patient rehabilitation stay.

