**Fig. 5 Fig5:**
[figure not shown]
Study procedure. The study duration for each participant is 3 weeks. Week 1 contains the familiarisation of the two versions of the exergame, two assessment blocks (Melbourne Assessment 2 and exergame tests) and the Test of Nonverbal Intelligence, Fourth edition (TONI-4). The TONI-4 will be planned before the first practice session day (i.e. on appointment 2 or 3). Week 2 contains three practice sessions with an assessment block proceeding the first practice session and another assessment block after the last practice session to evaluate immediate transfer and retention. One day after the last practice session, the assessment block is repeated to assess the delayed one-day transfer and retention). During week 3, the last assessment block is scheduled one week after the last practice session to assess the delayed 1-week transfer and retention. *TONI*-*4* Test of Nonverbal Intelligence, Fourth edition

##### Week 1

During the first appointment, the setup of the robot and the adjustments according to the child’s anthropometrics will be performed. This takes approximately 15 min. Each participant will then become familiarised with the two versions of the exergame. First, the transversal version ‘Unicorn’ will be played with manual guidance and verbal support from the therapist. Then, the transversal version ‘Snail’ will be played with only verbal guidance of the therapist. The same procedure will be followed for the exergame that is played in the frontal plane (i.e. ‘Submarine’ will be played with manual guidance and verbal support followed by ‘UFO’, which will be played with only verbal support). Subsequently, an assessment block consisting of the MA2_fluency_ [45] and an exergame test will be performed.

During week 1, also all the parameters for randomisation by minimisation will be obtained from the participant’s medical history (e.g. age, gender, diagnosis), from the attending occupational therapist (MACS level), and trained neuropsychologist (TONI-4). Participants will be characterised by age, gender, weight, height, diagnosis (including information about the affected side and specific features such as spasticity, dyskinesia or mixed condition) and the MACS level. After obtaining the minimisation parameters, participants will be allocated to their group.

##### Week 2

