On each of three consecutive days, all participants will practice 30 trials (15 trials of the horizontal and 15 of the vertical version of the exergame) in either a blocked or random order (according to their group allocation). Right before the first and after the last practice session, an assessment block will take place to assess the acquisition and immediate transfer and retention. One day after the last practice session, the assessment block will be repeated (1 day delayed transfer and retention).

##### Week 3

One week after the last training session, the assessment block will be repeated (1 week delayed transfer and retention).

The first session will include robot set-up and familiarisation and will be scheduled for approximately 75 min. Assessment blocks will take approximately 35 min and practice sessions 60 to 90 min. As the duration of an exergame trial depends on the child’s performance, it will vary largely and will affect the overall duration of the practice session. Once the robot settings have been adjusted to the participants’ anthropometrics, no additional set up time will be required. We defined an upper time limit of 120 min per session, which could be reached during practice sessions 1 and 3 that will also include a previous or subsequent assessment block. Sessions will be aborted after 120 min.

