##### Secondary outcomes

For all secondary outcomes, a multifactorial repeated measures analysis of variance (ANOVA) with ‘practice group’ and ‘time point’ as factors will be conducted over all the time points. A post-hoc analysis (Bonferroni correction for multiple comparisons) will be used to test for significant changes between the appropriate time points.

***Delayed transfers*** The MA2_fluency_ sum scores will be compared between the time point right before the first practice session, 1 day after the last session (1-day-delayed transfer), and 1 week after the last session (1-week-delayed transfer).

***Immediate retention, delayed retentions, acquisition*** For the several retention time points and the acquisition, the parameter nP_norm_ (obtained during the exergame tests and the practice sessions, respectively) will be evaluated. Comparisons will be made between the data obtained during the exergame tests right before the first practice session with the data from immediately after the last practice session (immediate retention), 1 day after the last practice session (1-day retention), and 1 week after the last practice session (1-week retention). For the acquisition, all the data points obtained during the practice trials will be compared.

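### The 2-day parallel-therapy check fits the immediate outcome but gives no comparable control for within-participant change over the 9 days of the 1-week delayed outcomes

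*Protocol article*

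**What the plan says.** The Protocol article has no usual-care arm. Under Feasibility outcomes, question 9, each child serves as his or her own control through the measurements in week 1. The abstract's Methods paragraph describes these as "two assessment blocks (robot-assisted reaching tasks, Melbourne assessment 2, subscale fluency), 2 days apart, take place".

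Item 9 under Analysis of feasibility uses all participants "to test for a significant change in exergame and MA2fluency scores between day 1 and day 3 in week 1", by paired t test or Wilcoxon signed-rank test. If week 1 shows no change, and therapy schedules in weeks 1 and 2 are alike, a change in week 2 may be ascribed to the robot. If week 1 shows improvement, week-2 changes are to be read with caution. Week 3 is not mentioned.

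The schedule under Study procedures is:
- Week 2: "On each of three consecutive days, all participants will practice 30 trials". "Right before the first and after the last practice session, an assessment block will take place", and a further block follows one day after the last session.
- Week 3: "the last assessment block is scheduled one week after the last practice session" (caption of Fig. 5).

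Under Secondary outcomes, the block before the first session is the reference for the comparison with the block "1 week after the last session (1-week-delayed transfer" (the label given there). The 1-week retention comparison is built the same way. The Setting section adds: "All measurements and practice sessions will be performed during a multidisciplinary in-patient rehabilitation stay".

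**The concern.** The no-practice data are the trial's only control for what inpatient therapy does without the robot. A window of 2 days says little about therapy gain that builds up over 9 days, and the 1-week outcomes are the ones most exposed to such gain. Item 9 also leaves unused a longer no-practice interval that the schedule already provides, from the week-1 blocks to the block just before the first practice session.

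At stake is how the pilot answers question 9. It could report no sign of therapy confounding from the 2-day check, and a reader could then carry that reassurance over to a pre-to-1-week change for which the check has little sensitivity. The answer also bears on how the main trial should control for parallel therapy.

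**Working it through.** **Spans that follow from the text**
- Control window, day 1 to day 3 of week 1: 3 − 1 = 2 days, as the abstract states.
- Immediate (primary) outcome, before session 1 to after session 3 on consecutive days: 2 days.
- 1-day delayed outcomes: 2 + 1 = 3 days.
- 1-week delayed outcomes: 2 + 7 = 9 days, which is 9/2 = 4.5 times the control window.

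**Unused no-practice interval (assumption)**

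The gap between weeks 1 and 2 is not stated. Assume consecutive weeks and weekday appointments only. The three practice days and the 1-day block need four consecutive weekdays, so practice starts on Monday or Tuesday. The first week-1 block falls on Monday to Wednesday and the second two days later. Then:
- first week-1 block to pre-practice block: 5 days (Wednesday to Monday) to 8 days (Monday to Tuesday);
- second week-1 block to pre-practice block: 3 to 6 days.

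If weekend appointments are allowed, the first of these ranges becomes 3 to 10 days.

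**Power of the check**

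Inputs:
- n = 20, all children pooled (Target sample size).
- Two-sided alpha 0.05, stated for item 10 and assumed for item 9.
- Minimal detectable change 2 points and minimal clinically important difference at least 3 points for the fluency subscale (Outcome measures).
- SD of a retest difference, assumed: 2/1.96 = 1.02 if the minimal detectable change is at the 95% level, 2/1.645 = 1.22 if at the 90% level (the level is not stated), and 1.5 and 2.0 as wider values.
- Therapy-only gain, assumed linear and equal to 2 points over 9 days.

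Drift in a window of w days = 2w/9: 0.44 points in 2 days, 1.11 in 5 days, 1.78 in 8 days. Power comes from the noncentral t distribution with 19 degrees of freedom and noncentrality drift × √20 / SD. For 2 days and SD 1.02 the noncentrality is 0.444 × 4.472 / 1.02 = 1.95.

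| SD | 2 days | 5 days | 8 days |
|---|---|---|---|
| 1.02 | 0.456 | 0.996 | >0.99 |
| 1.22 | 0.342 | 0.972 | >0.99 |
| 1.5 | 0.242 | 0.881 | 0.999 |
| 2.0 | 0.157 | 0.655 | 0.965 |

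**Sensitivity**
- If the 9-day drift were 3 points, the 2-day window would hold 3 × 2/9 = 0.67 points, with power 0.791, 0.643, 0.471 and 0.294 for the four SDs.
- The same four values apply to a 2-point drift seen over 3 days, since 2 × 3/9 = 0.67. So if the extra interval were as short as 3 days, the gain over the 2-day check would be modest.
- With 16 children, the 2-day check has power 0.371 (SD 1.02) to 0.132 (SD 2.0) for the 2-point drift.

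**The case against.** Much of the case on the other side stands.

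- **The window is right for the primary outcome.** Both span 2 days. A reader might infer that the check is mis-sized in general. The schedule does not support that.
- **The protocol does not credit week-3 change to the robot.** Item 9 speaks of week 2 only, on an assumption about weeks 1 and 2. A reader might infer that a 1-week gain will be ascribed to practice on the strength of the 2-day test. No sentence says so. What remains is that the 1-week outcomes have no matching check.
- **Randomisation protects the trial's main question.** Both arms receive inpatient therapy, so a drift common to both does not bias blocked versus random in expectation. A reader might infer that this comparison is confounded. It is not. Only change over time within participants is exposed, and the plan does include post-hoc comparisons between time points.
- **Question 9 does not rest on one test.** Changes in weeks 1 and 2 are to be compared, and the kind and number of other therapies recorded across study periods. Both help interpretation, but neither supplies a longer no-practice interval. The repeated-measures ANOVA is to cover all time points and might take in the week-1 blocks, yet the comparisons listed start at the pre-practice block.
- **The longer interval is not a clean control.** It is still likely to be shorter than 9 days, spans a weekend, varies between children and includes one more assessment exposure, which matters most for the exergame test.
- **Weight.** The pilot is expected to be underpowered, reports confidence intervals and makes testing of the motor learning outcomes conditional on power. An added contrast could be left to an analysis plan. Item 9, however, does specify its contrast, so the choice of window is a stated one and can be reviewed.

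**Conclusion.** The point holds within limits. Item 9 supports attribution over about 2 days. It suits the immediate outcome and is close to adequate for the 1-day outcomes (3 days), but it offers no comparable control for within-participant change in 1-week transfer and retention (9 days).

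The 2-day and 9-day figures follow directly from the schedule. The size of the gap is illustrative. For a linear therapy-only gain of 2 points over 9 days and 20 children, power is about 16% to 46% with the 2-day check, against about 65% to over 99% with a 5 to 8 day interval. This rests on the assumed drift, on an SD between 1.02 and 2.0, and on consecutive weeks with weekday sessions. The advantage of the longer interval requires gain that accumulates over time, and it shrinks if that interval is only 3 days.

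The primary outcome and the randomised comparison are unaffected. This is an inexpensive improvement to the answer to question 9, not a defect in the main analysis.

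**What to change.** In item 9:
1. Keep the day 1 to day 3 contrast, and state that it supports attribution only for the immediate and 1-day outcomes.
2. Add an estimate, with 95% CI, of the no-practice change from the week-1 blocks to the week-2 block before practice, for both the fluency subscale and the exergame measure. Report the days elapsed for each child.
3. Use that estimate as a supportive reference when interpreting within-participant 1-week transfer and retention, and state its limits: it is likely to be shorter than 9 days, spans a weekend and includes repeat-test effects.

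The cost is a few sentences and one extra contrast on assessments already scheduled, with no added visit or burden for the children.

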### Target sample size

Since the recruitment rate will be one of our feasibility criteria, we will recruit for 1 year and calculate the recruitment rate, taking into account the number of eligible and recruited participants, and complete datasets. Yet, the CONSORT 2010 statement extension to randomised pilot and feasibility trials recommends to give some rationale for the target sample size [27]. Based on our center’s numbers from past years and taking into account the inclusion criteria, we anticipate to recruit 20 participants (10 per group).

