#### Outcome measures

##### Outcomes of the main study

***Primary outcome: immediate transfer of the practiced skill*** We chose the Melbourne Assessment 2 subscale fluency (MA2_fluency_) as the primary outcome measure for the immediate transfer. The MA2 consists of the four subscales movement range, accuracy, dexterity and fluency [39] and is an adequate measurement for research and clinical use in children with cerebral palsy [40]. The intraclass correlation coefficient of the test-retest reliability of the MA2_fluency_ is 0.96 (95% confidence interval 0.90–0.99), the minimal detectable change is 2 points and the minimal clinically important difference is at least 3 points [40]. Concerning the concurrent validity, Pearson’s correlation coefficients between the MA2_fluency_ and other tests amounted to 0.67 (Bruininks-Oseretsky Test of Motor Proficiency, Second Edition, subtest 3, manual dexterity), 0.76 (Box and Blocks Test) and 0.40 (Paediatric Motor Activity Log–Revised, quality of movement) [40]. The responsiveness of the MA2_fluency_ is high, which is indicated by significant change scores and a high standardised response mean value of 1.84 [40].

From a clinical point of view and in line with literature (e.g. [9]), we consider the transfer to be an important aspect of learning. We hypothesise that MA2_fluency_ will improve when practicing the reaching movements. During the exergames, the participant will be instructed to reach the target by the most direct path, i.e. as fast as possible. This is in line with the MA2_fluency_ scoring criteria, which include jerkiness, tremor and/or reduced speed of movement [41].

Since we considered the MA2_fluency_ to be more sensitive to change instantly after the practice sessions due to the relatively short practice period and to avoid a potential loss to follow-up at later time points, we chose the immediate transfer as the time point of interest for the primary outcome.

One of three trained occupational therapists will score the MA2_fluency_ by analysing the video. The rater will be blinded for the participant’s group allocation, the time point of assessment and the randomisation code. The sum scores will be calculated and used for further analysis.

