##### Feasibility outcomes

In line with recommendations on reporting protocols of pilot and feasibility trials [26], we will apply the following ten specific feasibility criteria:
Are the chosen inclusion criteria specific enough to result in a sample of participants, which is suitable for this pilot study (e.g. are they able to play the exergame)?Is the recruitment rate feasible? Since the main randomised controlled trial would require a large number of participants, it is relevant to know the number of participants that will be recruited during a certain period.The number of children enquired for the study, number of participants recruited, number of complete datasets within 1 year will be recorded and used to calculate recruitment rates.Is the scheduling procedure feasible? The appointments will be planned for 3 weeks for each participant. The person conducting the exergame tests and the MA2_fluency_ always will need to be the same. The same will apply for the person instructing the child during the practice sessions. Absences of personnel (e.g. due to illness, holidays or part-time employment) and the children (e.g. due to illness or short-term planned medical appointments), as well as the availability of the robot and material for the MA2_fluency_ (i.e. whether they are not used for therapy at the time points of the measurements), will need to be considered. Information about whether it is possible to schedule rooms, persons involved and the robot and table for performing assessments will be noted.Is the randomisation procedure feasible? Experiences of the persons involved will be collected and evaluated to answer this question.Is the whole procedure feasible for the participants? The rather time-consuming procedure and the high number of repetitions might be difficult for at least some of the participants because of fatigue or lack of motivation to play the exergames so many times. Both reasons influence motor learning negatively. Therefore, it is important to determine whether the participants included in this study are able to comply the whole study procedure. Information about aborted or shortened sessions or other incidents and their reasons (e.g. pain or discomfort, fatigue) will be taken from the lab journal.Is the handling of the robot feasible? The ChARMin robot has been in use in the clinical and research area since 2015. Since it is a newly developed tool, it is important to evaluate its handling. Any technical issues will be noted and then retrieved from the lab journal.Is the handling of the large amount of data feasible? Information from the assessors and the analyst on the primary outcome will be used.Are the outcome measures responsive and sensitive enough within this setting? Responsiveness analysis of the assessment data will be performed.Is there a confounding influence of parallel therapies within the rehabilitation setting? As the study will be conducted during the inpatient rehabilitation stay, it is important to estimate whether parallel-applied therapies could confound the results. Since an additional control group following usual care would require a larger sample, we chose a design in which each participant acts as its own control and, therefore, we included control measurements during the first week of the study procedure.The changes in the outcomes between week 1 (control week) and week 2 (practice week) will be compared. The kind and number of additional therapies taking place during the different study periods will be recorded to increase the quality of reporting [44].Is it feasible to conduct the main trial with respect to the needed sample size calculated from the data obtained for the primary motor learning outcome? With the data of the primary outcome measure, we will calculate the required sample size for the main trial.

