#### Analysis of motor learning outcomes of the main trial

As recommended by the CONSORT extension to pilot and feasibility studies, we will report 95% confidence interval estimates of the motor learning outcomes [27], as the study will be most likely underpowered. Hypothesis testing will only be conducted if the recruited sample size is large enough to warrant sufficient statistical power.

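### The main-trial sample size is computed from the group difference observed in about 10 children per arm, so the answer to feasibility question 10 is close to uninformative

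*Protocol article*

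**What the plan says.** Feasibility question 10 asks whether the main trial is feasible given its required sample size. Under Feasibility outcomes the source of that size is stated: "With the data of the primary outcome measure, we will calculate the required sample size for the main trial".

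Under Analysis of feasibility, item 10 gives the formula n = (Zα + Zβ)² × 2σ² / (μ1 − μ2)². Its inputs are:
- Zα: "value for a significance level *α* = 0.05, which is 1.96".
- Zβ: "value for the power of 80%, which is 0.84".
- σ: "The pooled standard deviation of the pre-and post-intervention differences (both groups) is indicated by" σ.
- μ1: this "is the mean pre-post-intervention difference of the intervention group 1", with μ2 defined in the same way for group 2.

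The pilot's size is given under Target sample size: "we anticipate to recruit 20 participants (10 per group"). Item 10 attaches no confidence limit, target difference or sensitivity range to n. For the primary instrument, the outcome section cites a minimal detectable change of 2 points and says that "the minimal clinically important difference is at least 3 points". Item 10 uses neither figure.

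**The concern.** The effect in a sample size calculation should be the difference the main trial must be able to detect. Here it is an estimate from about 20 children, entered as though it were known. The article itself expects the pilot to be underpowered for this contrast and prefers confidence intervals for it, yet item 10 puts the same contrast into a formula that magnifies its error.

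A chance large difference would yield a small n and an underpowered main trial in children. A chance small difference would make a worthwhile trial look impossible. Because the difference is squared, a result favouring the wrong practice order gives the same n as one favouring the right order.

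**Working it through.** **Inputs from the article.** Zα = 1.96, Zβ = 0.84, 10 children per group, σ pooled over both groups (18 degrees of freedom). The article states no main-trial n, so there is none to reproduce. Its constants are correct for a two-sided 5% test at 80% power: (1.96 + 0.84)² = 7.84, and 7.84 × 2 = 15.68. With d = (μ1 − μ2)/σ, the formula is n = 15.68/d², which is the number **per group**.

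**Assumed.** The true standardised difference d, since the article gives none. Values of 0, 0.3, 0.5 and 0.8 are shown. Changes are taken as normally distributed.

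**Step 1: precision of the observed difference.** SE = σ√(2/10) = 0.447σ. The 95% confidence half-width is 2.101 × 0.447σ = 0.94σ. An observed d of 0.5 has a 95% interval of −0.40 to 1.38 (noncentral t). The interval includes 0, so n runs from 15.68/1.38², about 9 per group, to unbounded.

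**Step 2: behaviour of the rule.** Pilots of 10 per arm were simulated, with n = 15.68 × s²/(observed difference)², rounded up.

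| True d | n per group needed | Median n | 5th–95th percentile | Below half the need | Above double | Wrong sign |
|---|---|---|---|---|---|---|
| 0.3 | 175 | 108 | 13 to about 12,400 | 45% | 29% | 25% |
| 0.5 | 63 | 58 | 9 to about 5,500 | 34% | 34% | 13% |
| 0.8 | 25 | 24 | 6 to about 850 | 25% | 29% | 4% |

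The extreme upper percentile varies between simulation runs (5,350 to 5,700 at d = 0.5); the other figures are stable. The wrong-sign figure can be checked directly: Φ(−0.5/0.447) = 0.13.

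At d = 0.5 the computed n is within 25% of the correct value in only 12% of pilots. A main trial run at the computed n has true power below 50% in 33% of pilots. At d = 0 the median n is 166, and a quarter of pilots return 56 or fewer.

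**Step 3: taking only σ from the pilot.** With 18 degrees of freedom, the 95% interval for σ is 0.76 to 1.48 times its estimate. For a fixed target difference, n is then uncertain by a factor of 0.57 to 2.19. The 80% one-sided upper limit is √(18/χ²) with χ² at its 20th percentile, which is 1.18 × SD, or variance × 1.40. If absolute points are analysed, n per group = 15.68 × SD²/Δ², with assumed SDs:

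| SD (points) | Δ = 3 | Δ = 3, SD × 1.18 | Δ = 2 | Δ = 2, SD × 1.18 |
|---|---|---|---|---|
| 2 | 7 | 10 | 16 | 22 |
| 3 | 16 | 22 | 36 | 50 |
| 4 | 28 | 40 | 63 | 88 |
| 6 | 63 | 88 | 142 | 198 |

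**Step 4: scale.** Item 10 speaks of a pre-post difference. The primary analysis compares (MA2₄ − MA2₃)/MA2₃ between groups. In illustrative scenarios with assumed baselines, the choice of scale moves n by about 5% to 35%: 63 against 66 per group for baselines of 12 to 20 points, and 64 against 86 for baselines of 5 to 20.

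**The case against.** The formula and its constants are correct, and question 10 is only one of ten feasibility criteria. The article sets no threshold for n and no automatic progression rule, so the computed n would not by itself start or stop the main trial. It also says openly that the pilot is likely underpowered and commits to 95% confidence intervals. All of that stands. It limits the consequence, but it does not make the number informative.

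A reader might infer four stronger points, which the article does not support:
- **That the scale mismatch causes the noise.** It does not. The noise comes from the small pilot and the squared difference. Item 10 never says absolute or points, and it draws on the primary outcome, so relative change may be meant. What is supported is that the two sections need reconciling.
- **That n will be used as a total.** Read that way, power would fall from 80% to 51% (Φ(√(7.84/2) − 1.96) = 0.51). The article labels n only as sample size and nowhere calls it a total. This is an incomplete label.
- **That testing in the pilot is circular.** The article says: "Hypothesis testing will only be conducted if the recruited sample size is large enough to warrant sufficient statistical power". It does not say that item 10's formula, which is given for the main trial, judges this. No effect-size gate can be attributed to the plan.
- **That 3 points is the right target as it stands.** The article cites it as a property of the instrument, not as a difference between two active arms doing the same number of repetitions. It also applies only to an analysis in points.

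**Conclusion.** The concern holds for the effect entered in item 10. Feasibility question 10 rests on a number whose 5th to 95th percentile spans more than two orders of magnitude at every non-zero true effect examined. A true effect of zero can still look feasible. The size of the problem depends on the assumed true effect, on normal data and on the anticipated 10 per arm. The conclusion does not, because a standard error of 0.45 SD is large against any of the assumed effects. The per-group label and the wording of the scale are minor additions.

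**What to change.** Rewrite item 10 as follows:

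1. Replace (μ1 − μ2) with a prespecified between-group target difference on the scale of the main-trial primary analysis, and justify it for a comparison of two active arms. If absolute MA2 fluency points are analysed, the cited 3 points, with 2 as sensitivity, can be the starting anchor. If relative change is kept, state the target on that scale.
2. Take only σ from the pilot, for the same outcome and analysis, and use its 80% one-sided upper confidence limit (1.18 × SD with 18 degrees of freedom; recompute if the number of children differs).
3. Report n over a grid of target differences and SDs, and answer question 10 from that grid.
4. Label n as per group.
5. Reconcile item 10's pre-post difference with the relative difference in the primary analysis.
6. Report the pilot's observed difference with its 95% confidence interval, as already planned, but do not use it to set n.

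The cost is analysis wording only, with no extra children or assessments in the pilot. The downside is real: the upper limit for σ raises the planned n by about 40% compared with its point estimate (for example 16 to 22, or 36 to 50, per group). The sponsor must also defend a target difference in advance.
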